### Planned analyses and expected outcomes

In order to capture the contribution of covariates within both experiments, 3A and 3B dependent variables will be analysed under a generalized linear modelling framework based on a pre-specified decision tree (see Fig 3). The choice of link-function will be informed by the distributional properties of the data and the evaluation of standard model diagnostics (e.g., Q-Q plot of residuals) and indices of marginal likelihood (e.g., AIC). Nested model comparison will be used to evaluate whether model fit is significantly improved by the inclusion of focal parameters. Random effects and additional covariates accounting for potential sources of noise (e.g., mean inter-beat interval, time-on-task) may be included if warranted by theoretical considerations and model comparisons (for a similar approach, see [44]). As part of this analysis we will quantify microsaccades frequency and latencies, as well as pupil area trajectory. These findings will be included in the results and, if we find that any of these data features, when considering the period immediately following the cue, differ significantly between conditions we will include these as covariates in the model.

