*Experiment B: Does action improve sensitivity to backwards-masked stimuli?* This experiment combines MIB with a type of backward masking of the target stimulus. If the target is backwards-masked to preclude perception in the passive condition—by removing the target as it approaches the foveal region of the visual field—AI-C predicts that the target will still be perceived when the same masking setting is applied in the active condition. If there is no difference between conditions, or if the passive condition results in improved perceptual recognition, this would be evidence against AI-C; otherwise, this will provide evidence that action facilitates conscious awareness, and in that sense will predominantly support the active inference prediction.

Both experiments will also be equipped with measures of autonomic and neuromodulatory (i.e., cardiac and pupil) activity to adjust for any differences in attentional set (e.g., arousal) that could be considered to confound condition-specific differences. Further, in primates, attentional selective sampling under normal conditions is typically associated with motor activity (e.g., ballistic saccades or microsaccades, as well as eye blinks and pupil dilation and constriction), and therefore this study will record not only the saccades in the active condition (for play-back in the passive condition) but also microsaccades, pupil diameter and blinks throughout, in order to quantify differences between two conditions (such as microsaccades when fixating on the relevant location in both the passive and action conditions).

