### Operational hypotheses

The hypotheses being tested by the experiments described in this Study Protocol are as follows:

Experiment A: changes in conscious experience manifest earlier in the active than the passive condition, as measured by behavioural responses;

Experiment B: backward masking can preclude changes in conscious experience in the passive condition but not (as much) in the active condition.

These hypotheses stem from the putative role of active inference to confirm the sensory input expected following action (as described in the Introduction). Active sampling should promote faster resolution of uncertainty, engendering earlier perceptual inference. These hypotheses can be expressed in terms of the following predictions about the patterns of data we expect to observe in each experiment:

1]*Subjective report of reappearance of peripheral stimuli will occur after a shorter delay following subjective disappearance in the active vs. the passive condition of Experiment A* (see Table 1).2]*The psychophysical reappearance threshold for the radius of the masking boundary (once eye gaze is inside this invisible circular boundary the stimulus is masked) will be higher ; i.e., a larger radius in the active vs. the passive condition of Experiment B* (see Table 2).

**Table 1 pone.0328836.t001:** Predictions about the effect of active (vs. passive) sampling on target time-to-reappearance in Experiment A.

Theory	Decrease	No change	Increase	Confidence
IIT	X	X		Low
NREP	X	X		Medium
AI	X			High

**Table 2 pone.0328836.t002:** Predictions about the effect of active (vs. passive) sampling on mask onset boundary distance in Experiment B.

Theory	Decrease	No change	Increase	Confidence
IIT		X	X	Low
NREP		X	X	Medium
AI			X	High

Each of the other theories considered in the adversarial collaboration, IIT and NREP, offer different predictions to these, which also differ in their degree of confidence:

IIT is consistent with both manipulations (active or passive target sampling) quickly breaking suppression, by changing visual cortex state. Motor involvement (active) may be enough to tip the balance towards breaking suppression more easily, for a small difference in time to reappearance and/or masking boundary. Thus, for Experiment A (see Table 1), IIT predicts either decrease or no change, with low confidence; for Experiment B (see Table 2), IIT predicts either increase or no change, with low confidence.

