NREP is compatible with motor movement conveying arousing/attentional effects (other than via active inference), which may facilitate early detection. For instance, motor activity can profoundly stimulate V1 firing activity, and motor-associated arousal may help to detect stimuli at greater distance from foveation point. Thus, for Experiment A (see Table 1), NREP predicts either decrease or no change, with medium confidence; for Experiment B (see Table 2), NREP predicts increase or no change, with medium confidence.

In addition to the two main hypotheses, we also predict the following, based on AI-C, which is not part of the adversarial collaboration and thus do not elicit predictions from the competing theories:

3)
*In Experiment B target stimuli will be discriminated more accurately in active vs. passive trials given the same frequency of reappearance.*
4)
*In Experiment B confidence in target discrimination will be higher in active vs. passive trials given the same frequency of reappearance.*

In the setting of the overall adversarial collaboration (TWCF ARC INTREPID), these sets of predictions will be considered in conjunction with predictions from all theories on three main experiments, in total. The aspiration is that this total set of findings from all experiments will strongly distinguish among these three theories (even if individual experiments are not able to strongly distinguish them). Table 3 illustrates some of the main predictions and confidences of each theory for selected, key parameters for each experiment, with Experiment 3 being described in this study protocol (for full details, please see the preregistration).

**Table 3 pone.0328836.t003:** Illustration of predictions and confidences for each theory about each consortium experiment (for selected, key parameters); for the full prediction tables and specification of the parameters, please consult the INTREPID preregistration.

Experiment	IIT	NREP	AI-C
1	Confirm prediction, high confidence	Predict no change, high confidence	Predict no change, medium confidence
2	Confirm prediction, medium confidence	Confirm prediction or predict no change, high confidence	Predict no change, medium confidence
3	Confirm prediction or predict no difference, low confidence	Confirm prediction or predict no difference, medium confidence	Confirm prediction, high confidence

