An important factor, considered in the development of this study protocol, is the potential contribution of arousal in eliciting or promoting awareness, where arousal can take the shape of either phasic (stimulus-specific) or tonic (context-specific) arousal. In basic physiological terms, the role of arousal in psychophysical experiments such as those described here is well understood—specifically, that it enhances neural excitability and, depending on the level, may increase signal-to-noise ratios. Here, the locus coeruleus (LC) system mediates tonic and phasic arousal states affecting overall alertness, while phasic arousal helps fine-tune perception in response to specific stimuli. Studies using pupillometry have directly linked LC activity to changes in sensory processing, reinforcing the idea that arousal plays a major role in perception. All theories should thus expect these physiological processes to be in play, and understood as such the presence of arousal will not directly support one theory over the other. It will be a matter of further interpretation and modelling of the results to specify how arousal aligns with the core tenets of each theory. Here, it is of significance that, according to the active inference framework, arousal in this setting can be read in terms of attentional set and therefore reflects mental active inference, usually involving interoceptive inference [45–51]; this would make the arousal process an indispensable part of the active inference underpinning a change in consciousness. In contrast, for IIT and NREP, arousal would pertain to processes distinct from but interacting in important ways with the core processes posited by NREP and IIT as necessary for consciousness; this difference in outlook on arousal and attention partially explains the differences in the prediction table (shown above) for this experiment; that is, IIT and NREP’s predictions are not the opposite to those of AI-C, but partially overlap, and with weaker confidence. The interpretation of results, in particular differences of arousal between the two conditions, in the light of theoretical commitments will thus help situate the role of arousal and attentional set in diverse theories of consciousness. To help disambiguate the contributions of motor active inference (saccades) and mental active inference (i.e., attention and arousal) to perception, we opted to measure cardiac and pupil responses. Measuring inter-beat interval estimates allows us to adjust for context-specific arousal for a given trial. Pupillometric changes are considered integral to stimulus-bound aspects of active inference [51–53]. Cardiac and pupil data therefore allows us to quantify the contribution of (stimulus-specific and context-specific) attentional set and (saccadic) motor action to changes in perceptual content.

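### A significance test on post-cue pupil and microsaccade measures decides whether predictions 1 and 2 are tested on the total active-passive effect or on an effect net of part of its mechanism

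*Protocol article*

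**What the plan says.** Planned analyses and expected outcomes commits the team to a set of eye measures: "we will quantify microsaccades frequency and latencies, as well as pupil area trajectory". It restricts the comparison of these features to a window, "when considering the period immediately following the cue", and then fixes the consequence: if any of them "differ significantly between conditions we will include these as covariates in the model". The wording is firm. Other covariates, such as mean inter-beat interval and time-on-task, may be included if theory and model comparison support them; these will be.

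The protocol gives two accounts of what such measures represent. The Current study section introduces the cardiac and pupil recordings as a means "to adjust for any differences in attentional set (e.g., arousal) that could be considered to confound condition-specific differences". The Discussion says of arousal under the tested theory that "this would make the arousal process an indispensable part of the active inference underpinning a change in consciousness", and adds: "Pupillometric changes are considered integral to stimulus-bound aspects of active inference".

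The hypothesis for Experiment A is stated without any conditioning on eye measures: "changes in conscious experience manifest earlier in the active than the passive condition, as measured by behavioural responses". Prediction 2, for Experiment B, is likewise a plain active-passive difference in the masking-boundary threshold.

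**The concern.** The Main experiment paragraph for Experiment A has the cue release the saccade in active trials and instruct continued fixation in passive trials. The eye-tracking analysis steps then reject passive trials in which central fixation is lost between the cue and the end of the movement. Oculomotor behaviour after the cue therefore differs by design. A condition difference in that window is something the manipulation can produce, so it cannot be read as a pre-existing imbalance.

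The trigger selects the variables that condition has changed. If they also help determine when or whether the target reappears, adding them removes the part of the active-passive effect that passes through them. What remains answers a different question from predictions 1 and 2.

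Two consequences follow. First, the Current study section counts no difference in Experiment A strongly against AI-C, and no difference in Experiment B against it as well. A null reached by adjusting out part of the mechanism would be scored against the theory that proposed the mechanism. Second, Status and timeline has each lab develop and run its own pipeline. With a significance trigger, one lab could report a total effect and the other a partial one under the same label.

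**Working it through.** **Status of the covariates**

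- Timing: after the cue, hence after the manipulation (Planned analyses and expected outcomes).
- Role under AI-C: component of the mechanism (Discussion, both statements quoted above).
- Role under NREP: "NREP is compatible with motor movement conveying arousing/attentional effects (other than via active inference), which may facilitate early detection" (Operational hypotheses). This also places arousal downstream of the movement.
- Role in the Current study section: possible confounder.

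Two of the three theories' own accounts put these measures on the path from condition to outcome. Only the Current study section treats them as something to be adjusted away.

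**The plan's own figure**

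Inputs: n = 55, partial eta squared 0.13, power at least 80% (Participants, sample size, exclusion/inclusion criteria, and stopping rule); within-subjects contrast of two conditions (Experiment A, design). Alpha and sidedness are not stated, so two-sided 5% is assumed.

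- f² = 0.13 / (1 − 0.13) = 0.149
- dz = √0.149 = 0.387
- noncentrality = 0.387 × √55 = 2.87 on 54 degrees of freedom
- power (noncentral t) = 80.4%, and 55 is the smallest n that reaches 80%

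The stated sample size reproduces.

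**Effect of the rule**

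Let p be the share of the active-passive effect carried by the included covariates. The adjusted contrast is then dz × (1 − p).

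| p (assumed) | dz adjusted | power at n = 55 |
|---|---|---|
| 0% | 0.387 | 80% |
| 10% | 0.387 × 0.90 = 0.348 | 72% |
| 30% | 0.387 × 0.70 = 0.271 | 50% |
| 50% | 0.387 × 0.50 = 0.193 | 29% |

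The documents give no value for p, so this is a range and not an estimate. To restore 80% power for the adjusted contrast would take 67 participants at p = 10% and 213 at p = 50%.

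**Simulation check**

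Trial-level data were simulated for 55 participants with 72 trials per condition (the Experiment A section also gives 144; the choice does not affect the conclusion), 1,500 runs. The covariate was shifted by 0.5 trial-level SD between conditions and entered when its paired p-value fell below 0.05. The shift, the 5% entry level and the variance components are assumptions.

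- The rule included the covariate in 100% of runs.
- The ratio of adjusted to total effect was 1.00, 0.75, 0.50, 0.24 and 0.01 for p = 0, 25%, 50%, 75% and 100%.
- Power under the rule was 80%, 55%, 29%, 10% and 4%, while the unadjusted contrast stayed at 79 to 81%.
- With a shift of only 0.05 SD, the rule included the covariate in 19 to 20% of runs. Which effect is estimated is then largely a matter of sampling.

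**The case against.** The strongest reply is that adjustment is deliberate. The Experiment A design text places the emphasis on overt eye movement. The Discussion says the physiological measures are there to separate motor from mental active inference. NREP's rival account runs through movement-related arousal. A contrast net of arousal is what would set the saccade apart from that account, and on this reading the adjusted estimate is the wanted one.

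This stands as a reason to report such a contrast. It does not show that the contrast decides the hypotheses. Nothing in the protocol redefines predictions 1 and 2 as effects net of pupil or microsaccade change. If that were intended, the covariates would be in the model whatever their p-value.

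There is also partial mitigation. The Fig 3 caption puts a basic model at the top of a prespecified tree, the eye findings will be reported, arousal differences are to be interpreted by theory, and a committee oversees the analysis. None of these names the model without post-cue covariates as decisive.

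A reader might infer more than the documents support:

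- *That the estimate is certainly biased toward the null.* There is no loss if the covariates do not predict the outcome. If an unmeasured factor such as momentary attention drives both covariate and outcome, the distortion can go either way.
- *That collinearity alone costs substantial power.* Covariate-condition correlations of 0.5 and 0.7 give 1/(1 − r²) = 1.33 and 1.96, with power of 68% and 52%, but only if the active-passive effect does not vary between participants. When that variation is 1 to 4 times the trial-residual part (an assumption), power is about 74 to 78% at r = 0.5 and 64 to 73% at r = 0.7. The larger losses are upper-end figures.
- *That chance entry of covariates is a serious further problem.* A rate of 14 to 19% (1 − 0.95³ to 1 − 0.95⁴) assumes three or four independent tests at 5%, a level the protocol does not state. A feature that enters by chance differs little by condition and hardly moves the estimate.
- *That pre-cue pupil or inter-beat interval is a safe substitute.* Active and passive trials run in alternating blocks of 24, so participants can know the condition before the cue, and pre-cue arousal may also be affected by it.

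**Conclusion.** The point holds. The protocol fixes a rule under which a significance test on post-manipulation measures chooses between two different effects for the test of predictions 1 and 2. The protocol's own text gives those measures conflicting roles, and the two labs could end with different effects under one name.

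The size depends on the unknown mediated share: power at n = 55 is 80% at 0%, about 72% at 10%, 50% at 30% and 29% at 50%. This assumes a two-sided 5% test, the planned partial eta squared of 0.13 for the total effect, and no unmeasured common cause of covariate and outcome. Attenuation is the expected direction because both the AI-C and NREP accounts have arousal aiding detection, but it is not certain. The inconsistency in what is being estimated remains whatever the share.

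**What to change.** In Planned analyses and expected outcomes and in the decision tree:

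1. State that the condition contrast without any post-cue covariate decides predictions 1 and 2.
2. Delete the rule that a significant condition difference brings the pupil and microsaccade measures into the model.
3. Report pupil- and microsaccade-adjusted models as prespecified, labelled secondary mediation or sensitivity analyses, run whatever the size of the condition difference. This preserves the separation of motor from mental active inference that the Discussion seeks.
4. Use pre-cue pupil and inter-beat interval only in sensitivity analyses and do not call them baseline adjustment, because of the blocked design.
5. Reconcile the confounder wording in the Current study section with the Discussion.

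The cost is wording and a timestamped entry through the route in Dealing with amendments. No new data are needed and no planned analysis is lost. Data collection is already underway, so both labs should adopt the change before condition differences are examined.

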### Data management and sharing plan

The management of intellectual property will align with the guidelines from the European Commission and the guidelines of both institutions involved in the project, as will our policy for sharing physiological, behavioural, and eye tracking data. Specifically, we will adhere to the European Commission’s open access and data management policy and the European Commission’s Grants Policy on sharing of unique research resources.

All investigators agree to willingly share data and materials associated with this project so as to expedite future discoveries in consciousness and maximise the study’s impact. Following the acquisition of data, all data and any subsequent analysis will be uploaded to a shared server available to all team members, as well as all members of the consortium and its associated committees. Over the life of the project analysis and findings based on these data will be shared through multiple media, such as (including but not limited to) media appearance, lab meetings, conference talks, and seminars (both at the host institutes and with the broader national and international scientific community).

In line with the principles of open science, de-identified data will be made available on an appropriate data repository. The specific items to be made publicly available as part of our resource sharing plan include:

All R/ Matlab/ Python code used for stimulus creation, manipulation, and experiment presentation, as well as all code used to pre-process or analyse the data.All (de-identified and PHI removed) physiological, eye-tracking, and behavioural data adhering to FAIR data principles. Despite creating no neuroimaging data in this arm of the project, the larger TWCF project will be organised to align with the Brain Imaging Data Structure BIDS format (http://bids.neuroimaging.io). All metadata will be made available.Any peer-reviewed publication (the TWCF ARC initiative mandates open access publications).

To allow the reuse of data—whilst also ensuring its integrity—downloading parties will be required to register before downloading any demographic, behavioural, eye tracking, or physiological data. A condition of the registration is that users agree: 1) not to distribute the data to third parties; 2) not to attempt to identify study participants; 3) to properly acknowledge the data resources. Data will be converted to shareable data formats (BIDS) and machine-readable annotations of the task and R/Matlab/Python scripts detailing the purpose of components will be included. There will be a GITHUB repository linked to the primary EBRAINS (or an equivalent alternative) repository that will be made available at the completion of the INTREPID project. We will review all data prior to upload to ensure they do not contain personal information or identifiable features. Data will be stripped of these details and will be General Data Protection Regulation (GDPR) compliant. We will share unprocessed (ASCII), minimally processed and final processed (CSV) data. All custom code and analysis pipelines will be shared. The experiment will be made available following publication via the OSF platform which links the user with all data being shared via EBRAINS (https://ebrains.eu/).

## Discussion

The study protocol addresses key behavioural commitments of a hypothesis about changes in conscious content derived from the active inference framework, contrasted in an adversarial collaboration with predictions derived from a predictive processing-based theory (NREP) and from Integrated Information Theory (IIT), neither of which posits action as a necessary condition on change in conscious experience. The Study Protocol therefore forms one of four Study Protocols (to be published separately) for this adversarial collaboration consortium (with two protocols for Experiment 2) as part of the INTREPID consortium project. Briefly, the prediction is that active inference—as enacted in overt eye-movement—will facilitate a change in conscious perception more than a passive condition, in a paradigm where a stimulus first made invisible through motion-induced blindness becomes consciously perceived. The contrasting, passive condition is where there is no overt action and where the change in conscious perception should be delayed or precluded.

An important factor, considered in the development of this study protocol, is the potential contribution of arousal in eliciting or promoting awareness, where arousal can take the shape of either phasic (stimulus-specific) or tonic (context-specific) arousal. In basic physiological terms, the role of arousal in psychophysical experiments such as those described here is well understood—specifically, that it enhances neural excitability and, depending on the level, may increase signal-to-noise ratios. Here, the locus coeruleus (LC) system mediates tonic and phasic arousal states affecting overall alertness, while phasic arousal helps fine-tune perception in response to specific stimuli. Studies using pupillometry have directly linked LC activity to changes in sensory processing, reinforcing the idea that arousal plays a major role in perception. All theories should thus expect these physiological processes to be in play, and understood as such the presence of arousal will not directly support one theory over the other. It will be a matter of further interpretation and modelling of the results to specify how arousal aligns with the core tenets of each theory. Here, it is of significance that, according to the active inference framework, arousal in this setting can be read in terms of attentional set and therefore reflects mental active inference, usually involving interoceptive inference [45–51]; this would make the arousal process an indispensable part of the active inference underpinning a change in consciousness. In contrast, for IIT and NREP, arousal would pertain to processes distinct from but interacting in important ways with the core processes posited by NREP and IIT as necessary for consciousness; this difference in outlook on arousal and attention partially explains the differences in the prediction table (shown above) for this experiment; that is, IIT and NREP’s predictions are not the opposite to those of AI-C, but partially overlap, and with weaker confidence. The interpretation of results, in particular differences of arousal between the two conditions, in the light of theoretical commitments will thus help situate the role of arousal and attentional set in diverse theories of consciousness. To help disambiguate the contributions of motor active inference (saccades) and mental active inference (i.e., attention and arousal) to perception, we opted to measure cardiac and pupil responses. Measuring inter-beat interval estimates allows us to adjust for context-specific arousal for a given trial. Pupillometric changes are considered integral to stimulus-bound aspects of active inference [51–53]. Cardiac and pupil data therefore allows us to quantify the contribution of (stimulus-specific and context-specific) attentional set and (saccadic) motor action to changes in perceptual content.

At a later stage of this overall project, the findings from this experiment will be considered in conjunction with further computational modelling and electrophysiological responses acquired with EEG or MEG (and further no-report iterations of these experiments). Computational modelling—under active inference—will elucidate the underlying computational mechanism giving rise to the hypothesised difference in behavioural responses and furthermore generate time resolved synthetic neuronal responses for comparison with empirical responses. EEG and MEG versions of the study will use frequency tagging techniques [54,55], which allows time-resolved tracking of stimulus-bound neural activity. Theoretically, such further grounding in computational modelling and neuronal data will address questions about the neurophysiological implementation of active inference in its own right (i.e., not in an adversarial setting) and, in particular, the coordination of motor action and mental action during active sensing. These studies will aim to distinguish top-down and bottom-up signals so as to characterise the time course of their propagation in the process of perceptual reappearance in motion induced blindness.

